### Investigational product

2.7

AV2^®^ is a synergistic combination of FDA-approved organic compounds, having a highly effective broad-spectrum anti-viral effect, both topically as orally. It is a mixture of natural essential oil components (carvone, eugenol, geraniol, nerolidol) in equal volumes diluted 50% in olive oil (Olea europea).

The components of AV2 have a long history of use in the Food and Fragrance industry. The components earned the GRAS (Generally Recognized As Safe) status in 1965. The present FDA status of the components is the following: Carvone: GRAS under 21 CFR 182.60; Eugenol: “Direct Food Substances Affirmed as Generally Recognized as Safe” status under 21 CRF 184.1257; Geraniol: GRAS under 21 CFR 182.60; Nerolidol: “Food Additives Permitted for Direct Addition to Food for Human Consumption”” status by FDA under 21 CFR 172.515 [13], [14], [15].

It is postulated that AV2^®^ de-activates the HPV virus outside the cell by preventing endocytosis. Due to the broad-spectrum antiviral activity of AV2^®^, cervical lesions may regress due to deactivation of the virus. (8). It is administered as a topical spray to the cervix.

*Side effects:* Topically AV2^®^ does provoke for about 30–60 s a warming or burning feeling similar to disinfecting alcohol on very sensitive areas such as *Labia minora*.

*The Placebo* consists of 10% lemon (*citrus limon*) and 10% lime (*citrus aurantifolia*) essential oils in 80% olive oil. The oils are included to provide a fragrance to the placebo, similar to AV2^®^.

### Outcomes

2.8

-The primary outcome will be the change of lesions 2 months after randomization.

Change of lesions will be defined as regression or progression of the size of the lesion seen on VIA. Regression can be partial or complete when there is a total disappearance of the lesion also called remission. On cytology, regression will be defined as improvement from high-grade to low-grade CIN and remission will be defined as improvement from any grade of CIN to no CIN.

-The secondary outcomes will be:The secondary outcomes will be•Clearance of HPV at 2 months post-randomization,•Correlation between change of lesions change in HPV DNA at 2 months post-randomization,•Change in HPV viral particle load 6 months post-randomization.-The tertiary outcome will be the number of patients with adverse effect.

An adverse effect (AE) will be defined as any unfavourable and unintended sign, symptom, or disease temporally associated with the use of the product administered. A causality assessment of the AEs will be done in accordance with the guidelines of the WHO–Uppsala Monitoring Centre.

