### Procedures and follow-up (Fig. 1)

2.3

Prior to the start of the study, a basic training of the doctors and nurses involved will be organized. This training will encompass Good Clinical Practice (GCP), collection of liquid-based cytology sample with cytobrushes, and VIA and cryotherapy procedures.

Women aged 25 and over will be invited to participate in a community cervical cancer screening programme. After giving their informed consent, eligible women will be examined by a trained doctor. The procedure will be performed while the woman lies in the lithotomy position on the examination table. After the cervix is exposed by a speculum inserted in the vagina, the doctor will collect a LBC specimen using the Thinprep PreservCyt solution^®^ (Hologic, Marlborough,USA), immediately after LBC sampling, VIA will be performed. Its results will be reported according to the WHO criteria and will serve for randomization. The results for LBC and HPV testing will not be available at this moment.

VIA-negative women will not be randomized and will receive no treatment. VIA-positive women will be randomized to one of two groups to receive either AV2^®^ or placebo. All randomized women will be followed-up and recalled after two months for repeat LBC and VIA. Women remaining positive on VIA at this stage will be treated by cryotherapy.

At six months' follow-up, women will be assessed in the same manner regarding VIA and LBC. The study will end at this stage. At each stage, the examinators will be blind to the previous results concerning the patient. At the end of the study, All women who will test positive for cervical lesions or HPV will be properly treated according to standard protocols and resources.

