### Visual inspection of the cervix with acetic acid

2.5

VIA involves the painting of the cervix with 5% acetic acid and the observation of the color change 1 min after. The most common form of reporting the VIA test outcome involves negative and positive categories, depending upon the absence or presence of acetowhite lesions and clinical signs of invasive cancer. A positive test is generally based on the detection of well-defined, densely opaque acetowhite lesions in the transformation zone closer to the squamocolumnar junction. The criteria for a negative test includes one or more of the following: no acetowhite lesions, faint ill-defined translucent acetowhite lesions, endocervical polyps, nabothian cysts, dot-like acetowhite lesions, acetowhite lesions far away from the transformation zone and a prominent squamo-columnar junction.

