### Methods for LBC samples

2.6

It is not possible to perform HPV testing locally as there are no laboratory facilities in DRC allowing this. Laboratory examinations will be done at the HPV and STIs Training Centre for Africa, Sefako Makgatho Health Sciences University, Pretoria, South Africa. To ensure quality, all the samples will be re-examined at Algemeen Medisch Laboratorium (AML) in Antwerp, Belgium.

From a single LBC specimen collected in the ThinPrep test vial containing the PreservCyt^®^ solution, both cytology and HPV testing will be performed. HPV testing in this study will encompass both HPV detection and HPV genotyping as well as HPV viral particle load. Cytology results will be reported according to the 2001 Bethesda system terminology.

Sample collection

The HPV and STIs Training Centre for Africa will receive Thinprep vials with 10 ml of the cervical sample. The samples will be stored at room temperature between 15 °C and 30 °C in a store room. The level 2 safety hood is set up and prepared by cleaning with alcohol followed by DNASe away for decontamination. The vials will be moved to dirty area (extraction room) for preparation. The pipettes will also be cleaned with alcohol and DNASe away for decontamination. The 2 ml tubes will be labeled according to the sample number on the ThinPrep vials. A 1000 μl pipette will be used to remove 2 ml of sample from the ThinPrep vials into the 2 ml test tubes for HPV testing avoiding any spillage or aerosol. The ThinPrep vials will be then filled to the ThinPrep vial mark (10 ml) with Preservcyt solution to prepare for cytology slide processing. The ThinPrep vials will then be capped and stored at room temperature until processing of the cytology slides on ThinPrep T5000 system.

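### Section 2.8 does not fix one primary outcome: VIA lesion size and cytological grade sit side by side with no size measure, no cut-off and no rule for which decides

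*Protocol article*

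**What the plan says.** Section 2.8 (Outcomes) names a single primary outcome: "The primary outcome will be the change of lesions 2 months after randomization". It then explains the term: "Change of lesions will be defined as regression or progression of the size of the lesion seen on VIA". Shrinkage short of disappearance is included: "Regression can be partial or complete when there is a total disappearance of the lesion also called remission". The next sentence of the same paragraph turns to the smear: "On cytology, regression will be defined as improvement from high-grade to low-grade CIN". Cytological remission is then defined as going from any CIN grade to none.

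Four other places bear on how this would be scored.

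- Section 2.5, on VIA: "The most common form of reporting the VIA test outcome involves negative and positive categories". It lists criteria for a positive and a negative test but no size scale.
- Section 2.3, on VIA at screening: "Its results will be reported according to the WHO criteria and will serve for randomization". At 2 months, women still VIA-positive go to cryotherapy. On the readers: "At each stage, the examinators will be blind to the previous results concerning the patient".
- Section 2.6, on the smear: "Cytology results will be reported according to the 2001 Bethesda system terminology".
- Section 2.9 powers the trial on one lesion regression rate, 50% v 70% at 2 months, and does not say which regression is meant.

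**The concern.** A primary outcome should give each woman one value that any analyst would reproduce. Here at least three success rates fit the text: complete disappearance on VIA, any shrinkage on VIA, and improvement on cytology. They need not agree in the same woman, and they do not share a denominator. Entry is by VIA alone, before cytology is known, so some randomized women may have no CIN on cytology at baseline and nothing to improve from under the second rule.

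Choosing among these readings after the data are seen could change the trial's conclusion. It also leaves the sample size unanchored: 50% and 70% may be plausible for one definition and not for another, and a reader cannot tell which was meant.

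**Working it through.** **1. The text, side by side**

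| Needed to score it | What the article gives |
|---|---|
| Complete VIA remission: positive at entry, negative at 2 months | Available (2.3, 2.5) |
| Partial VIA regression, or progression: a size at both visits and a cut-off | No unit, method or cut-off |
| Cytological change: a grade at both visits on the scale of the rule | Rule in CIN grades, reporting in Bethesda terms, no mapping stated |
| Precedence between VIA and cytology | Not stated |

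The Introduction shows that a cut-off was within reach: the cited phase 2 trial reported lesion size reduced by more than 50%. Section 2.8 does not adopt it.

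**2. Effect on the denominator**

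Let g be the share of randomized women with no CIN on baseline cytology (not given in the article). Over all randomized women, cytological improvement cannot exceed 1 − g. A 70% rate is therefore out of reach if g is above 30%, and a 50% rate if g is above 50%. No such ceiling applies to VIA, because every randomized woman is VIA-positive at entry.

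**3. The plan's own sample size**

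Inputs: p1 = 0.50, p2 = 0.70 and power 95% (2.9); two-sided 0.05 (2.10); equal arms (2.9). With d = p2 − p1 and p̄ = (p1 + p2)/2:

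n0 = [1.960·√(2p̄(1−p̄)) + 1.645·√(p1(1−p1) + p2(1−p2))]² / d²

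n = (n0/4)·[1 + √(1 + 4/(n0·d))]² (continuity correction)

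At 50 v 70%, p̄ = 0.60, n0 = 152.95 and n = 162.8, so 163 per arm. This matches section 2.9, so the arithmetic is sound. Evaluable per arm after 10% loss: 190 × 0.9 = 171.

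**4. Complete remission, if the 20-point difference holds**

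| Rates | n per arm |
|---|---|
| 50 v 70% | 163 |
| 40 v 60% | 170 |
| 30 v 50% | 163 |
| 20 v 40% | 144 |
| 10 v 30% | 111 |

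All lie within 171.

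**5. Complete remission, if partial responders drop out of the success count**

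Suppose 50% and 70% include partial regressions, and a share f of regressions is partial, equal in both arms. The complete-remission rates are then 0.50(1−f) and 0.70(1−f), and the difference shrinks to 0.20(1−f). The article does not give f, so this is a range of assumptions. Power uses 171 per arm and the same continuity-corrected formula, solved for power.

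| f | Rates | n per arm for 95% | Power with 171 |
|---|---|---|---|
| 0 | 50 v 70% | 163 | 96% |
| 10% | 45 v 63% | 208 | 90% |
| 25% | 37.5 v 52.5% | 297 | 77% |
| 50% | 25 v 35% | 563 | 48% |

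Without the continuity correction the last three powers are 92%, 80% and 52%.

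**The case against.** The best defence is that this is a condensed article. Section 2.5 describes the usual way of reporting VIA, not everything recorded, and section 2.3 defers to WHO criteria that are not set out. A size field may exist in the full protocol or on the case report form. Section 2.9 speaks of a regression rate, so the powered direction is stated, and the cytology sentence could be read as explaining terms for the repeat smear. That reading is possible, but the paragraph does not say so. A size field alone would settle neither the precedence nor which definition the rates belong to.

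A reader might infer more than the text supports, in four ways:

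- *That the outcome cannot be scored at all.* Complete VIA remission can be.
- *That blinded readers make shrinkage impossible to judge.* Sizes recorded separately at each visit can be compared later by someone else.
- *That Bethesda reporting is incompatible with the cytology rule.* The article does not list the Bethesda categories, and wording in high and low grade may map onto them. What can be said is that no mapping is stated. That low-grade women can only remit is not a defect, since remission is itself a favourable result.
- *That cryotherapy contaminates the 2-month result.* It follows the 2-month VIA reading, so it does not alter that outcome. Nor does section 2.3 call these women failures, and a partial response with residual disease is a coherent category. What remains is a wording conflict: a shrunken but still VIA-positive lesion is a regression in 2.8 and a persistent lesion in the abstract and 2.3.

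It is also fair that complete remission is not the only cure. Any single definition with a stated cut-off would remove the ambiguity.

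**Conclusion.** The point stands in limited form. Section 2.8 puts two non-equivalent definitions under one primary outcome, gives no precedence, and counts partial change without a measure or cut-off. Section 2.9 is tied to neither definition. Followed as written, this yields different regression rates and different denominators from the same women, which is more than omitted detail.

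The sample-size arithmetic is correct. Whether the planned size suits a clear definition depends on what the 50% and 70% were meant to include. It does if complete remission keeps a 20-point difference. It does not reach the planned 95% power if even 10% of those regressions are partial in each arm. The article gives no partial share, and its being equal across arms is an assumption, so the power figures are a range and not an estimate. It would be wrong to infer that moving to complete remission is free in sample size, and equally wrong to infer that the trial is underpowered.

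The article gives the trial's status as recruiting, so the definition should be settled before unblinding.

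**What to change.** - **Primary outcome.** Before unblinding, name one binary VIA-based outcome at 2 months, read before any cryotherapy. VIA-negative (complete remission, yes/no) is the one scorable from data already collected.
- **Partial shrinkage.** Make it secondary, from a size recorded at each visit, compared centrally and with a stated cut-off.
- **Cytology.** Make it secondary, with a stated mapping from Bethesda categories to the grades used, restricted to women abnormal at baseline.
- **Sample size.** State in 2.9 that the two rates refer to the chosen definition, and restate the power for it.
- **Wording.** Reconcile 2.8 with the abstract and 2.3 on lesions that shrink but stay VIA-positive. This concerns the outcome terms only; the treatment rule is not at issue here.

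The cost is a rewording of 2.8 and 2.9 and, if none exists, one size field on the VIA form. Women already seen without a recorded size could not contribute to the shrinkage outcome. The real price is statistical: complete remission is a stricter success, so observed rates will be no higher and may be lower than with partial shrinkage counted. If the difference narrows with them, the sample size may have to be reconsidered or lower power accepted.

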### Sample size

2.9

Assuming a lesion regression rate of 50% in the non-interventional group and 70% in the antiviral drug group at 2 months post-treatment, a minimum sample size of 163 patients is needed to show with 95% power a difference between both groups. To allow for up to 10% drop-outs or unevaluable patients, we will recruit at least 190 patients in each arm. We expect 20% of the women to be HPV positive, of whom 10% with and 10% without lesions, indicating that over 1900 women will have to be enrolled to obtain the required sample size.

### Statistical analyses

2.10

Data will be double-entered and cleaned in EpiInfo (version 6.04 b, Centers for Diseases Control and Prevention). Proportions will be compared using the x^2^ or Fisher's exact tests (when required). Student's *t*-test will be used for continuous variables. A Mc Nemar or paired *t*test will be used for within-patient comparisons where approriate. Non-normally distributed variables will be transformed, or nonparametric tests (Wilcoxon or Kruskal-Wallis) will be used. Stepwise multivariate analyses will be performed, and all possible interactions up to order 2 will be tested. All reported *P* values will be 2-sided. For all statistical analyses a *P* value of ≤0.05 will be considered as statistically significant.

All analyses will be performed using the STATA statistical analysis software packages (Version 12; Stata Corp, Lakeway, College Station, Texas, USA).

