### Randomization and blinding

2.4

VIA positive women will be randomized in a block wise manner, without stratification, to one of two treatment arms as shown in Fig. 1. Patients and study investigators will have no knowledge of the treatment arm allocation. To maintain blinding, active drug and placebo glass containers will be identical in appearance and scent. Patients and investigators will be unblinded only in the event of a suspected serious adverse reaction.

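### A cheap gain, not an error: lesion regression is compared unadjusted, although baseline HPV and cytology, sampled before randomisation, could be fixed as strata in the primary test

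*Protocol article*

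**What the plan says.** Section 2.10 (Statistical analyses) lists tests by type of variable. For proportions it says "Proportions will be compared using the x^2^ or Fisher's exact tests (when required". It does not assign a test to the primary outcome by name. However, section 2.9 (Sample size) treats that outcome as a proportion: "Assuming a lesion regression rate of 50% in the non-interventional group and 70% in the antiviral drug group at 2 months post-treatment". The chi-square or Fisher test is thus the only stated between-arm comparison that fits it.

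Section 2.4 (Randomization and blinding) says "VIA positive women will be randomized in a block wise manner, without stratification". Section 2.3 (Procedures and follow-up) places the liquid-based cytology sample immediately before VIA, and hence before randomisation, and says of that point: "The results for LBC and HPV testing will not be available at this moment". Section 2.6 has cytology and HPV testing done on that one specimen. The Discussion expects results some months later.

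Section 2.10 also says "Stepwise multivariate analyses will be performed, and all possible interactions up to order 2 will be tested". It names neither the outcome nor the candidate covariates of these models.

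**The concern.** Randomisation admits every VIA-positive woman, whatever her HPV or cytology status. The Discussion says that randomising only HPV-positive women would have been ideal and lists reliance on VIA as a limitation. If placebo regression differs by baseline HPV or cytology, a chance imbalance in that mix passes straight into an unstratified difference.

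The results arrive too late to stratify randomisation but not too late to stratify the analysis. Because the specimen predates randomisation, conditioning on it keeps all randomised women and does not disturb the type I error. What is at stake is precision, not validity.

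The stepwise models do not supply this. They are not tied to the primary comparison, and the data choose their covariates.

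**Working it through.** **1. The plan's own figure.** Inputs from sections 2.9 and 2.10: 50% v 70%, two-sided alpha 0.05, power 95%.

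- Pooled formula: [1.960 × √(2 × 0.6 × 0.4) + 1.645 × √(0.5 × 0.5 + 0.7 × 0.3)]² / 0.2² = (1.358 + 1.116)² / 0.04 ≈ 153 per arm.
- With continuity correction: (152.95 / 4) × [1 + √(1 + 4 / (152.95 × 0.2))]² = 162.8, so 163.

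The stated 163 is reproduced exactly, as a per-arm number. With 10% loss, 163 / 0.9 gives 182, which the planned 190 covers; 190 × 0.9 = 171 evaluable. Power of the uncorrected chi-square is about 96% at 163 per arm and about 97% at 171. The sizing is sound.

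**2. Gain at the planned effect.** Simulation of 20,000 trials per scenario, 163 per arm, two baseline strata. The poorer-prognosis stratum holds 30%, 50% or 70% of women. A common odds ratio keeps the overall rates at 50% and 70%. The stratum shares and placebo gaps are assumptions.

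| Placebo gap between strata | Chi-square power | CMH power | n per arm with CMH equivalent to 163 |
|---|---|---|---|
| 0-10 points | about 96% | about 96% | 163-164 |
| 20 | about 96% | about 96.5% | 158-159 |
| 30 | about 96% | about 97% | 151-154 |
| 40 | about 96% | 97.4-98.1% | 141-147 |
| 50 | about 96% | 98.2-98.9% | 128-139 |

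Type I error is about 5% for both tests. The gain is 0 to about 3 points.

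**3. Gain if the effect is smaller, with imperfect markers.** HPV and cytology only approximate the underlying prognostic status. Take two groups of about equal size, a placebo gap d between them and overall regression near 50%. A perfect marker removes a share d² × 0.25 / 0.25 = d² of the variance. A marker with 85% sensitivity and specificity shrinks the visible gap to (0.85 + 0.85 − 1) × d = 0.7d, so it removes (0.7d)²:

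- d = 20 points: 0.14² = 2.0%
- d = 40 points: 0.28² = 7.8%
- d = 60 points: 0.42² = 17.6%

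Suppose the unadjusted test has 80% power, so its expected z is 1.96 + 0.84 = 2.80. Dividing by √(1 − share removed) gives 2.83, 2.92 and 3.09. Subtracting 1.96 gives power of about 81%, 83% and 87%.

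Simulation agrees. With 171 per arm and AV2 adding 15 points in everyone, 80% rises to 83% (gap 40) and 87% (gap 60). With AV2 adding 20 points only in the 52.6% assumed to have a true lesion (0.526 × 20 = 10.5 points overall), 49% becomes 50%, 52% and 55% at gaps of 20, 40 and 60. A single marker with 70% sensitivity and specificity gains only about 0, 1 and 2 points in that setting.

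**4. The recommended four cells.** Simulating HPV × cytology with imperfect markers gave gains of roughly 0-1 point at a gap of 20, 2-4 at 40 and 4-10 at 60. Type I error was about 5%, and essentially nothing was lost when the strata were not prognostic.

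**The case against.** The strongest reply is that nothing here is wrong. An unstratified test after unstratified block randomisation is valid and matches the sizing. Section 2.10 is a short generic list in a condensed article, choice of covariates is commonly left to an analysis plan, and the mention of multivariate models shows that adjustment is not excluded. Most of this stands. It makes the point an improvement rather than an error. It does not remove it, because the article does state its tests and its only route to adjustment is data-driven.

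Three stronger readings are tempting, and the documents do not support them.

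- **The primary test is underpowered.** A reader might infer this from power near 49% when AV2 works only in true lesions. That figure comes from diluting the overall effect to about 10.5 points, not from using a chi-square, and stratifying recovers little of it. Large gains need both a perfect marker and extreme assumed gaps.
- **Nearly half the randomised women are VIA false positives on the protocol's own figures.** The sum is 0.08 × 0.9 / (0.8 × 0.1 + 0.08 × 0.9) = 0.072 / 0.152 = 47%. It combines a VIA accuracy quoted in the Introduction for a CIN2 threshold with a share of HPV-positive women with lesions of unstated grade from section 2.9. A CIN1 lesion could be a false positive under the first and a lesion under the second.
- **The gain costs nothing and every woman has a baseline value.** Some samples may be invalid, and section 2.6 has all samples re-examined at a second laboratory, so someone must decide whose result counts.

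Nor does the article give regression rates by HPV or cytology. It says only that much HPV infection and mild dysplasia may regress without treatment, which does not fix the size of any gap.

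**Conclusion.** The point holds as an inexpensive improvement. The stated comparison is valid and correctly sized. It leaves unused two baseline measurements that the trial collects anyway and that may be prognostic. The benefit is small if the planned effect is real and modest if the effect is smaller and baseline status predicts regression well; with gaps of 20 points or less it is negligible.

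These sizes rest on assumed stratum shares, placebo gaps and marker accuracy, since the article supplies none of them. The conclusion that a fixed stratified test is safe does not depend on those values: type I error stayed at about 5%, and essentially no power was lost when the strata carried no information.

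**What to change.** In section 2.10, and in the analysis plan:

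- Name the primary test as a Cochran-Mantel-Haenszel test of lesion regression at 2 months by arm, in all randomised women, stratified by baseline high-risk HPV (positive/negative) and baseline cytology (normal/abnormal).
- Fix these two factors in advance and take no covariate for the primary comparison from the stepwise models.
- State which laboratory's result defines the strata, and give invalid baseline samples their own stratum.
- Report the stratum-adjusted risk difference with its 95% confidence interval.
- Keep the plain chi-square as a sensitivity analysis.

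The cost is a sentence or two of text, with no new data, visits or participants. The primary analysis must wait for the baseline laboratory results, which the HPV outcomes already require, and the rule for invalid samples has to be written before unblinding. The sample size need not change.

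### The 6-month viral-load change is compared between arms without assured adjustment for baseline viral load, which the trial already measures; within-patient tests should be labelled descriptive

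*Protocol article*

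**What the plan says.** Section 2.8 (Outcomes) makes lesion change at 2 months the primary outcome: "The primary outcome will be the change of lesions 2 months after randomization". It lists "Change in HPV viral particle load 6 months post-randomization" among the secondary outcomes.

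Section 2.10 (Statistical analyses) lists tests by type of variable and ties none of them to a named outcome:
- Proportions are compared by chi-square or Fisher's exact test.
- Student's t "test will be used for continuous variables". Non-normal variables are transformed or given a Wilcoxon or Kruskal-Wallis test.
- A McNemar or paired t "test will be used for within-patient comparisons where approriate".
- Stepwise multivariable analyses are planned, with interactions up to order 2.
- A two-sided threshold of 0.05 applies to all analyses.

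The baseline value exists. Section 2.3 has the liquid-based cytology sample taken at entry, immediately before VIA, and section 2.6 has viral load measured as part of HPV testing on that sample.

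**The concern.** Viral load varies between women, and a woman's entry value is likely to predict her later value. A t-test on the change score subtracts the whole baseline value, whatever the actual correlation. ANCOVA estimates how much of it to remove. The comparison as written therefore gives a wider interval than the same data allow. Stepwise selection is no substitute, because whether baseline enters would depend on the data.

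A second, smaller matter is the status of the within-patient tests. The 0.05 threshold covers them, and nothing says that they are descriptive. Section 2.3 says that "VIA-positive women will be randomized to one of two groups to receive either" AV2 or placebo, so every randomised woman is VIA-positive at entry. A within-arm McNemar test on VIA can then move in one direction only. The Discussion itself expects much HPV infection and mild dysplasia to regress spontaneously, so a within-arm P value would partly measure natural history. At 6 months it would also include the effect of cryotherapy given to women still VIA-positive at 2 months.

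**Working it through.** **1. The plan's own figure.** Section 2.9 assumes regression of 50% and 70% and states that "a minimum sample size of 163 patients is needed to show with 95% power a difference between both groups". Take p1 = 0.5, p2 = 0.7, mean 0.6, difference 0.2, two-sided alpha 0.05 and power 95%.

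- Without continuity correction: n' = [1.960·√(2·0.6·0.4) + 1.645·√(0.25 + 0.21)]² / 0.2² = (1.358 + 1.116)² / 0.04 ≈ 152.95, so 153 per arm.
- With continuity correction: n = (n'/4)·[1 + √(1 + 4/(n'·0.2))]² = (152.95/4)·(1 + 1.0634)² ≈ 162.8, so 163 per arm.

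The stated 163 is reproduced exactly. It is a comparison of two independent proportions, so the primary outcome was sized as a between-arm test.

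**2. Variance of the viral-load comparison.** The article gives neither the SD nor the correlation r between entry and 6 months. Assume equal SD σ at both times and r from 0.3 to 0.7.

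- t-test on change: 2σ²(1 − r)
- ANCOVA: σ²(1 − r²)
- Ratio: (1 − r²) / [2(1 − r)] = (1 + r)/2

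| r | Change score (σ²) | ANCOVA (σ²) | Ratio | Less variance | Narrower interval (1 − √ratio) |
|---|---|---|---|---|---|
| 0.3 | 1.40 | 0.91 | 0.65 | 35% | 19% |
| 0.5 | 1.00 | 0.75 | 0.75 | 25% | 13% |
| 0.7 | 0.60 | 0.51 | 0.85 | 15% | 8% |

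The direction does not depend on equal variances. With SDs σ1 and σ2, the change-score variance minus the ANCOVA variance is σ1² + σ2² − 2rσ1σ2 − σ2²(1 − r²) = (σ1 − rσ2)², which is never negative.

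**3. What this means for power (illustration).** Assume a true difference of 0.3σ and 163 evaluable women per arm. Power = Φ(0.3/(s·√(2/163)) − 1.96), where s is the square root of the tabled variance.

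| r | t-test on change | ANCOVA |
|---|---|---|
| 0.3 | 63% | 81% |
| 0.5 | 77% | 88% |
| 0.7 | 94% | 97% |

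Viral load is informative only in women HPV-positive at entry. Their number among randomised women is not stated, so 163 is an upper-end illustration. The variance ratios in step 2 do not depend on it.

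**4. Within-arm tests.** If all discordant VIA pairs go one way, the exact two-sided McNemar P is 2·(1/2)^k for k women who convert. Five give 0.0625 and six give 0.031. So six conversions in the placebo arm are enough to reach the threshold.

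For a paired test in one arm of 163 with no drug effect, a spontaneous mean change of 0.1, 0.2 or 0.3 SD of the change would be declared significant in 25%, 72% or 97% of trials (normal approximation).

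**The case against.** The strongest reply is that the article is condensed, an analysis plan may exist, and covariate adjustment and the status of secondary tests are commonly settled there. A t-test on change is also valid under randomisation and does use the baseline value. Rank tests, which section 2.10 allows, cope with undetectable loads better than a logarithm does. All of this stands. It limits the point to a better method than the one named, for one secondary outcome. It does not remove the point, because section 2.10 does name an unadjusted test and the better one needs no new data.

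Three stronger readings are tempting, and the documents do not support them.

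- *The change outcomes will be judged by within-patient tests that ignore the placebo arm.* Section 2.10 assigns no test to any outcome and qualifies the paired tests as used where appropriate. The sample size rests on a difference between groups ("Assuming a lesion regression rate of 50% in the non-interventional group and 70% in the antiviral drug group"), and chi-square or Fisher's exact test is planned for proportions.
- *At 50% regression, about 86 of 171 placebo women (190 × 0.9 = 171) would turn VIA-negative, giving a McNemar chi-square of 86.* Section 2.8 says "Change of lesions will be defined as regression or progression of the size of the lesion seen on VIA", and regression may be partial. A woman with partial regression may remain VIA-positive and is then not a discordant pair. The article gives no VIA conversion rate, so that figure does not follow.
- *Paired tests are degenerate throughout.* This applies to VIA, which defines entry. Cytology and HPV results were not known at randomisation, so they can change in either direction.

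**Conclusion.** The point holds in a limited form. As written, the between-arm comparison of 6-month viral-load change has no assured baseline adjustment, although the baseline is collected. Against a t-test on change, ANCOVA would reduce the variance by 35%, 25% or 15% at correlations of 0.3, 0.5 or 0.7. These sizes rest on assumed correlations and equal variances. The gain over a rank test was not calculated. Baseline adjustment does not deal with cryotherapy given between 2 and 6 months.

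The lack of a statement that within-patient tests are descriptive is a matter of clarity. Nothing in the article shows that they are meant as evidence of efficacy. The primary comparison of regression proportions and its 163 per arm are unchanged.

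**What to change.** - Analyse log10 viral load at 6 months between arms by ANCOVA, with treatment arm and baseline log10 viral load both forced into the model, in women HPV-positive at baseline. That subset is defined before randomisation, so the comparison stays randomised.
- Set undetectable loads to a value at the assay's detection limit, stated in advance on the reporting scale. Women who clear HPV otherwise have no logarithm.
- Give a rank-based ANCOVA as a sensitivity analysis, since many values may tie at that limit.
- Keep the stepwise models exploratory for this outcome.
- State that efficacy conclusions rest on the between-arm comparisons used for the sample size, and that within-patient changes are reported descriptively, without P values.

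The cost is wording in the analysis section or analysis plan, best settled before unblinding. No new data, visits or women are needed.
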